## Abstract

**Background:**

Educational and self-care measures are important for women after gynecological pelvic cancer treatment. Pelvic floor muscle training exercises (PFMT) are a conservative treatment for pelvic floor (PF) dysfunction. The purpose is to evaluate the impact of a telerehabilitation and self-care program on PF dysfunctions, reports of urinary incontinence (UI), and physical–emotional factors of participants post-treatment for gynecological pelvic cancer.

**Methods:**

Two-arm randomized clinical trial: an intervention group (IG) will evaluate the effect of a telerehabilitation program on women undergoing clinical practice of radiotherapy for the treatment of gynecological pelvic cancer and a control group (CG) will maintain the routine. Primary outcome is the prevalence of reports of UI, which will be assessed using the International Consultation on Incontinence Questionnaire—Short Form (ICIQ-SF). The secondary outcomes will be the severity and impact of UI on quality of life, location and perception of pain intensity, presence and intensity of dyspareunia, vaginal stenosis, fecal incontinence (FI), and levels of physical activity. Statistical analysis will be performed by intention-to-treat, and multivariate mixed effects analysis will be used to compare results.

**Discussion:**

Activities in the context of telerehabilitation using PFMT and self-care can represent a viable and effective solution to minimize the side effects of gynecological cancer treatment and improve women’s quality of life.

**Supplementary Information:**

The online version contains supplementary material available at 10.1186/s13063-024-08138-1.

## Background

Advances in treatment for gynecological pelvic cancer have improved women’s survival, but as a side effect, the risk of pelvic floor (PF) dysfunction has increased [1, 2]. A systematic review showed that the main PF dysfunctions after treatment of gynecological neoplasms are urinary incontinence (UI), fecal incontinence (FI), and sexual dysfunctions [3]. Other PF dysfunctions include vaginal stenosis [4], pelvic pain [5], and decreased muscle function [6]. This type of cancer sensitizes a woman’s feminine identity, as it causes sexual dysfunctions [5, 7–9], dyspareunia [6–8], low self-esteem [8, 10], decreased quality of life [7, 8], and decreased physical activity [11, 12].

It is found in the literature through a systematic review that pelvic floor muscle training exercises (PFMT) is the first line of treatment for UI [13], in improving sexual function [14, 15], and in vaginal stenosis [16]. PFMT is defined as an exercise to improve strength, endurance, power, and relaxation or a combination of these factors [17]. It is certified in the literature on telerehabilitation using PFMT in the treatment of PF dysfunctions and promoted a significant improvement in urinary symptoms, PFM function, and quality of life [18].

Telerehabilitation has become increasingly common, the availability and accessibility of care for women who live far from rehabilitation centers becoming increasingly viable [19]. It is important to highlight that telerehabilitation has educational and self-application objectives that require the development of educational support material that is suitable for the virtual environment. Educational videos and applications have great potential to contribute to virtual care, but there are few materials of this type specifically designed for this purpose that have been tested for their usefulness prioritizing a physical activity plan and self-care measures to contribute to a better quality of life for women [20].

Considering that cancer pelvic is currently among the health problems in the world, and its treatment contributes to PFM dysfunctions such as UI, it is urgent to investigate in high-quality RCTs new low-risk interventions capable to optimize the results obtained through telerehabilitation. Thus, this protocol study aims to evaluate the impact of a telerehabilitation and self-care program on PF dysfunctions, reports of UI, and physical–emotional factors of participants post-treatment for gynecological pelvic cancer.

## Methods

### Study design

Randomized and controlled, two-arm blinded evaluator clinical trial was designed to evaluate the effect of a telerehabilitation program in women undergoing clinical practice of radiotherapy and brachytherapy of gynecological pelvic cancer on the primary outcome of the prevalence of reports of UI, which will be evaluated using the following question from the International Consultation on Incontinence Questionnaire—Short Form (ICIQ-SF) “how often do you lose urine?”.

Secondary outcomes will be the severity and impact of UI on quality of life, sexual function, FI, self-esteem, quality of life, location and perception of pain intensity, presence and intensity of dyspareunia, vaginal stenosis, and physical activity levels. Finally, the intervention group will respond about treatment satisfaction, adherence to supervised sessions, home guidance through home diary recording, recording of adverse effects, and System Usability Scale.

Participants will be randomized to an intervention group that will participate in a telerehabilitation program or control group. This protocol will be reported according to the Protocol Items Standard: Recommendations for Intervention Trials checklist (SPIRIT) 2013: items recommended for a clinical trial protocol and related documents. It is a superiority trial.

### Ethic

This study will be carried out in accordance with the Declaration of Helsinki (1975) and was approved by the Ethics Committee for Research with Human Beings (CEPSH) of the Hospital das Clínicas of the Faculty of Medicine of Ribeirão Preto under protocol no. 4,718,873 and Committee Ethics Committee of the Oncology Research Center (CEPON) under protocol no. 5,013,364 and registered in the Brazilian Clinical Trials Registry (ReBEC) no. RBR-8ht5nqq.

For ethical reasons, we did not plan to prohibit any concomitant treatment. We included in the “Methods” section our plan to monitor any concomitant treatment for PF dysfunctions including UI, but we expect to have homogeneous groups in relation to these variables provided by an adequate randomization and sample size.

Figure 1 shows the CONSORT (Consolidated Standards of Reporting Trials) flowchart, enrollment schedule, interventions, and study evaluations. Figure 2 shows the checklist using the SPIRIT (Standard Protocol Items: Recommendations for Interventional Trials) used in the study (Additional file 1).

**Fig. 1 Fig1:**
[figure not shown]
The flowchart for selecting women for the randomized clinical trial, following the CONSORT

**Fig. 2 Fig2:**
[figure not shown]
Study evaluation schedule (SPIRIT). Source: According to the SPIRIT 2013 statement: Standard Protocol Item Definition for Clinical Trials

### Participants

The study will consist of participants diagnosed with gynecological pelvic cancer living in the State of Santa Catarina who underwent treatment at the Oncological Research Center—CEPON in Florianópolis, Santa Catarina, Brazil.

The principal investigator ([name]) will have access to a telephone list of women who have completed radiotherapy and/or brachytherapy treatment for gynecological pelvic cancer in the years 2020 to 2022. This researcher will contact these participants by telephone and ask “how often do you lose urine?” Participants with UI will receive an explanation of the stages of the study, and after consenting to participate, they will sign a consent form and then be taken for an individual interview with a scheduled day and time for data collection via google meeting; these interviews will be carried out with the researchers ([name] or [name]). In addition to the institution’s routine procedure, a physiotherapy session every 3 months for 5 years is included. During these sessions, the physiotherapist provides guidance on PFMT and the use of vaginal dilators.

### Eligibility criteria

The study will consist of participants with UI after radiotherapy and/or brachytherapy for gynecological pelvic cancer who underwent treatment at the Oncological Research Center—CEPON in Florianópolis, Santa Catarina, Brazil.

Women are defined as inclusion criteria: age group over 18 years old; clinical stages I to III of gynecological pelvic cancer; having undergone surgery, radiotherapy, and/or brachytherapy; reporting stress UI, urgent UI, or mixed UI (self-reporting by the question Short Form (ICIQ-SF) “how often do you lose urine?”); do not have orthopedic or neurological limitations that prevent the practice of the telerehabilitation program; and not undergoing physiotherapeutic treatment.

### Criteria of discontinuing

The criteria of discontinuing the trial for a given participant include withdrawal of consent to participate.

### Sample size

G*Power 3.1.9.2 software was used to calculate the sample size based on the difference between two means using the *T*-test, after a 12-week pilot study with 20 participants, 10 in the control group (CG) (2.8 ± 1.9) and 10 in the intervention group (IG) (1.41 ± 1.50). The variable considered for the calculation was the prevalence of UI through the ICQ (short-form) question “how often do you lose urine?” The answer is presented in the form of a Likert scale.

Taking these observations into account, a total number of 58 participants (29 IG and 29 CG) will be needed to detect a difference between the groups in the ICQ-SF question “how often do you lose urine?” after 12 weeks of intervention, assuming an alpha level of 0.05 and 80% power of the test.

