### Assessment

#### Primary outcome measures

The primary objective of this study will be to evaluate the impact of a PF telerehabilitation program on the prevalence of reports of UI in participants post-radiation therapy treatment for gynecological pelvic cancer. UI is the primary outcome at all times of the study, that is, baseline and after 12 weeks of intervention. Therefore, could the intervention of an educational telerehabilitation program promote improvements in reports of UI in these participants?

The prevalence of UI will be assessed using the following question from the International Consultation on Incontinence Questionnaire—Short Form (ICIQ-SF). “How often do you lose urine” being 0—never, 1—once a week or less, 2—two or three times a week, 3—once a day, 4—several times a day, and 5—how long all.

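### The stated pilot inputs give 25 per arm for 80% power, not 29, and the intervention-arm pilot mean of 1.41 is impossible for ten whole-number answers

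*Protocol article*

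**What the plan says.** The Sample size section of the protocol article describes one complete calculation. The method is given in the words "software was used to calculate the sample size based on the difference between two means using the" t-test, run in G*Power 3.1.9.2. The inputs come from a 12-week pilot of 20 women: "10 in the control group (CG) (2.8 ± 1.9) and 10 in the intervention group (IG) (1.41 ± 1.50"). The error rates are set by "assuming an alpha level of 0.05 and 80% power of the test". The result is that "a total number of 58 participants (29 IG and 29 CG) will be needed to detect a difference between the groups".

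The variable is the single ICIQ-SF question on how often urine is lost. The section on primary outcome measures gives its coding, "being 0—never, 1—once a week or less, 2—two or three times a week, 3—once a day", and continues in whole numbers up to 5.

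The article does not state whether the test is one-sided or two-sided; the Study design section says only "It is a superiority trial". The Sample size section mentions no allowance for loss and no correction for a rank test.

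**The concern.** The section gives the method, both means, both SDs, alpha, power and the answer, so a reader can repeat the calculation. Repeated as described, it gives a different number. That leaves open what 58 means. If a loss allowance was added, 58 is the number to randomise and about 50 are needed for analysis. If a rank-test correction or a higher power was used, 58 is the number to analyse.

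The second problem lies in an input. A mean of whole-number answers from ten women moves in steps of 0.1, yet the intervention mean is printed as 1.41. This is the article's only justification of the trial's size, so an input that cannot be right as described needs checking at its source.

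**Working it through.** **Inputs** (all from the Sample size section unless noted)
- Control pilot arm: n = 10, mean 2.8, SD 1.9.
- Intervention pilot arm: n = 10, mean 1.41, SD 1.50.
- Alpha 0.05, power 80%, equal arms.
- Sidedness is not stated. Two-sided is assumed; one-sided is also shown.
- Item coding: whole numbers 0 to 5 (primary outcome measures).

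**Effect size**
- Difference: 2.8 − 1.41 = 1.39.
- Pooled SD: √((1.9² + 1.5²)/2) = √((3.61 + 2.25)/2) = √2.93 = 1.712.
- d = 1.39/1.712 = 0.812.

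**Attempt to reproduce 29 per arm.** Power of the two-sample t-test is taken from the noncentral t distribution, with 2n − 2 degrees of freedom and noncentrality d√(n/2).

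| n per arm | Power, two-sided 0.05 |
|---|---|
| 24 | 78.6% |
| 25 | 80.3% |
| 29 | 86.0% |

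The smallest n reaching 80% is 25 per arm, or 50 in total. The normal approximation, n = 2(1.960 + 0.842)²/d² = 23.8, gives 24. A simulation that allows unequal variances (Welch test) gives 80.2% at 25 and 85.9% at 29, so the difference between the SDs is not the explanation. A one-sided test needs 20 per arm, which is further from 29.

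**Routes that could lead to about 29, none of them stated**
- 85% power instead of 80%: 29 per arm.
- A rank test at its minimum relative efficiency of 0.864: 79.0% at 28 and 80.4% at 29, so 29 per arm.
- A 15% increase on 50: 50 × 1.15 = 57.5, rounded up to 58.
- An intervention mean of 1.5: d = 1.30/1.712 = 0.759, with 79.7% at 28 and 81.1% at 29, so 29 per arm.
- SD 1.9 in both arms comes close without matching: d = 1.39/1.9 = 0.732 needs 31 per arm by the t-test, and it discards the stated SD of 1.50.

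**Check of the pilot mean.** Ten whole-number answers sum to a whole number, so their mean is a multiple of 0.1. The nearest possible values are 1.4 (sum 14) and 1.5 (sum 15). The smallest number of answers whose mean rounds to 1.41 is 17 (24/17 = 1.412). The control mean of 2.8 is possible (sum 28).

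**Effect of the doubtful input.** With 1.40, d = 1.40/1.712 = 0.818 and power is 79.2% at 24 and 80.9% at 25, so still 25 per arm. With 1.5 the answer is 29, as shown above.

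**Margin in 58 if the stated inputs stand.** Fifty evaluable women keep 80% power, so (58 − 50)/58 = 13.8% can be lost.

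**The case against.** The strongest reply is that an adjustment was probably made and left out of a condensed article. The stated means, SDs, alpha and power give exactly 29 per arm under a rank test at minimum efficiency, and 15% added to 50 gives 58. This stands as a possible explanation, and it means that 58 should not be called a wrong recruitment target. It does not remove the point, because the section names a t-test and says 58 are needed for 80% power. The absence of a loss allowance is not a separate complaint.

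A second reply is that the consequence is small and in the safe direction. That is right as long as the pilot values are right. A third is that 1.41 may be a typing slip for 1.4, with almost no effect. That may be so, but 1.5 is the other neighbouring value and it changes the answer from 25 to 29.

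Three stronger readings are tempting and are not supported:
- A reader might take the SD of 1.50 as further evidence of misreporting. With a mean of 1.4, ten answers can have an SD of 1.497 when the divisor is n, which prints as 1.50. The article does not say which divisor was used.
- A reader might infer that the pilot did not measure the planned outcome. The section names the item, and the control values of 2.8 and 1.9 are both attainable on it.
- A reader might infer that the trial is underpowered. Power is 77% with 23 per arm (about 20% loss) and 71% with 20 per arm (about 30% loss), but the article gives no loss rate. These figures are illustrations only.

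**Conclusion.** The point holds in two parts. First, the stated inputs require 25 per arm for 80% power two-sided, or 20 one-sided, not 29; with 58 analysed, power is about 86%. This assumes the named t-test and the pooled SD, and either sidedness leaves the mismatch. If the pilot values are right, the discrepancy is conservative. Second, the intervention mean of 1.41 cannot come from ten answers on this item, whatever test is used, so the mean, the n or the variable is misreported. The article does not show which. Nothing here shows that the trial is too small, but the statement of size and power should be corrected because the trial's size rests on it.

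**What to change.** 1. Check the pilot data and correct the intervention mean, SD and n, or name the variable they describe.
2. Only then rerun the calculation. Report the sidedness, any rank-test correction or loss allowance actually used, and whether 58 is the number randomised or the number evaluable.
3. If the stated inputs are confirmed in substance, say that 25 evaluable women per arm give 80% power (two-sided 0.05, t-test), and that 58 gives 86% with no loss and keeps 80% with up to about 14% loss.

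The wording in step 3 should not be adopted before step 1 is done, because a corrected mean of 1.5 would make 29 per arm the right answer without any allowance for loss. The cost is a look at 20 pilot records and one rewritten paragraph. The number recruited need not change unless the corrected pilot data show a smaller effect than 29 per arm can detect.

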### Statistical analysis

Data will be de-identified, encoded, and stored in the database using the Excel Program. The software SPSS 22.0 will be used for the analysis of data. The description of quantitative variables will be expressed in mean, standard deviation, minimum value, median, and maximum value. Qualitative variables will be described in absolute and relative values (%). For all primary and secondary results, a 95% confidence interval and a significance level of 0.05 will be considered in the test. Both per-protocol and intention-to-treat analysis will be performed.

A linear mixed-effect model will be used to analyze the ICIQ-SF score, FSFI score, FIQL score, EORTC score, IPAQ score, ROSEMBERG score, and System Usability Scale. In the reassessment, individuals’ values will be considered random effects, and the groups, the times, and the interaction between them will be regarded as fixed effects. In addition, the McNemar test will verify changes in categories variables before and after the intervention. Both per-protocol analysis [21–23] and an intention-to-treat analysis will be also conducted. The Cohen effect size (*d*) will be calculated using the averages.

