### Data collection

Data collection will be previously scheduled with participants online via Google Meet. The questionnaires will be applied in an interview format and will last 60 min; a researcher will receive training beforehand for data collection and will not participate in the intervention. The questionnaire covers general and clinical information, UI, sexual function, self-esteem, pain, dyspareunia, FI, and quality of life. All data collection will take place in two moments, firstly, in the period before the start of the intervention, called baseline (T0), and at the moment after the first stage of the intervention, that is, after the initial 12 weeks (T1) (Fig. 1).

Data collection from the control group will be carried out using the same questionnaires applied to the intervention group. Collection will be scheduled with the participants and will take place at the same interval as the intervention group.

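### With two assessments, the mixed model's group-by-time term is a change-score comparison, which is generally less precise than adjusting for the baseline already collected

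*Protocol article*

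**What the plan says.** The Statistical analysis section assigns a linear mixed model to the ICIQ-SF score, FSFI, FIQL, EORTC, IPAQ, Rosenberg and System Usability Scale scores. Participants enter as random effects, and "the groups, the times, and the interaction between them will be regarded as fixed effects". The section mentions neither a baseline covariate nor a constraint that the arms share a baseline mean.

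The Data collection section limits the data to two assessments: "All data collection will take place in two moments, firstly, in the period before the start of the intervention" (T0), and then after 12 weeks (T1). Table 2 shows a baseline value for every listed outcome except treatment satisfaction and the System Usability Scale.

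The Sample size section rests on another comparison. It is "based on the difference between two means using the" t-test, applied to the single ICIQ-SF frequency item, with pilot values of 2.8 ± 1.9 (control) and 1.41 ± 1.50 (intervention). It concludes that "a total number of 58 participants (29 IG and 29 CG) will be needed", "assuming an alpha level of 0.05 and 80% power of the test". It uses no baseline term and no T0–T1 correlation.

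**The concern.** When a model has only two time points and leaves the group, time and interaction terms free, it estimates a separate baseline mean for each arm. Randomisation makes those means equal in expectation, so estimating a baseline difference spends information. The interaction becomes the difference in mean change. Adjusting for baseline uses the same data and generally gives a narrower confidence interval.

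In a trial of 58 participants the difference can matter. At a low T0–T1 correlation, the change-score comparison can even be less precise than the 12-week t-test used to set the sample size. A low correlation is conceivable for the frequency item, because entry requires leakage and this restricts the baseline range. The same restriction would also tend to reduce the baseline SD, which works the other way, so both have to be varied in the check.

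**Working it through.** **Inputs.** From Sample size: means 2.8 and 1.41, SDs 1.9 and 1.50, 29 per arm, alpha 0.05, power 80%. Assumed, because the document does not state them: a two-sided test, pilot values that are 12-week scores, complete data, the T0–T1 correlation rho, and the ratio k of baseline SD to follow-up SD.

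**The plan's own figure.** The difference is 2.8 − 1.41 = 1.39. The pooled SD is √((1.9² + 1.50²)/2) = √2.93 = 1.712, so d = 1.39/1.712 = 0.812. An exact two-sided t-test with 80% power needs 25 per arm, 50 in total. The stated 58 is therefore larger than its inputs require, and at 29 per arm the 12-week t-test has 86.0% power. That is a separate matter from this point, but it means the trial starts with some reserve.

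**Variances**, in units of the variance of the T1-only comparison:
- difference in mean change (the interaction): 1 + k² − 2·rho·k, which is 2(1 − rho) when k = 1;
- baseline-adjusted difference at T1: 1 − rho², whatever k is.

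The first minus the second is (k − rho)². The change score is therefore never the more precise of the two on this measure, and the two are equal only when k = rho. With k = 1 the ratio is 2(1 − rho)/(1 − rho²) = 2/(1 + rho): 1.54 at rho 0.3, 1.33 at 0.5 and 1.18 at 0.7. With k = 0.8 it is 1.16/0.91 = 1.27 at rho 0.3 and 0.84/0.75 = 1.12 at 0.5.

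**Power**, if the model is applied to the frequency item. The noncentrality is d·√(29/2) divided by the square root of the variance factor, and d·√(29/2) = 0.812 × 3.808 = 3.09. At rho 0.3 and k = 1 this gives 3.09/√1.4 = 2.61 for the interaction and 3.09/√0.91 = 3.24 for the adjusted analysis. Noncentral t (56 df for the interaction, 55 df after adjustment):

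| rho | interaction, k = 1 | interaction, k = 0.8 | baseline-adjusted |
|---|---|---|---|
| 0.2 | 67.1% | 75.3% | 87.3% |
| 0.3 | 72.9% | 80.6% | 89.0% |
| 0.4 | 79.2% | 86.0% | 91.2% |
| 0.5 | 86.0% | 91.2% | 93.9% |
| 0.6 | 92.5% | 95.8% | 96.7% |

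**Where the interaction falls below 80%.** This happens when its variance factor exceeds about 1.18. With k = 1, 2(1 − rho) = 1.18 gives rho of about 0.41. With k = 0.8, 1.64 − 1.6·rho = 1.18 gives about 0.29. With k = 0.6, 1.36 − 1.2·rho = 1.18 gives about 0.15.

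**The case against.** The strongest reply is that the power figures may belong to a variable the model does not cover. The effect size and the 29 per arm come from the single frequency item, which is the primary outcome. The mixed model is assigned to the ICIQ-SF score, and the article defines the total score as a sum of three questions, listed among the other outcome measures. Applying the model to the frequency item is an inference, so the power figures are conditional on it. The precision argument does not need that inference: it holds for every quantitative scale that the model covers and that is measured at both times.

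A second reply is that a change-score comparison is valid, unbiased and in common use. This is right. With equal SDs and a correlation of 0.5 or more, it is at least as powerful as the t-test the trial was sized on. What remains is a loss of precision against a better use of the same data, not an error.

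A third reply is that the equal-SD figures are the least favourable in the range examined, k from 0.6 to 1. This also stands, and it is why the results for k = 0.8 are given beside them.

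A reader might also infer that the plan is at fault for not naming the coefficient that answers the question. The text lists fixed effects and does not declare the interaction to be the treatment test. The same model can also give the between-arm difference at T1. Naming the reported contrast is detail that an article commonly leaves to the analysis plan, so its absence here is no finding.

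**Conclusion.** The point holds as one of precision. As specified, with two assessments and complete data, the group-by-time term is the difference in mean change, and it is generally less precise than a baseline-adjusted comparison. With equal SDs the variance is 54% larger at a correlation of 0.3, 33% larger at 0.5 and 18% larger at 0.7. The penalty is smaller if the baseline SD is moderately below the follow-up SD, and it vanishes when the SD ratio equals the correlation.

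It would be tempting to conclude that the trial is underpowered for its planned analysis. The documents do not support that. A fall below 80% requires that the model is used for the frequency item, that the interaction is the reported test, that the pilot values are 12-week scores, and that the correlation is low: below about 0.41 with equal SDs, or about 0.29 at an SD ratio of 0.8. Neither the correlation nor the baseline SD is given. The shortfall is possible, not established. Baseline adjustment is therefore recommended as a free improvement.

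**What to change.** For the frequency item and each quantitative scale measured at both T0 and T1, replace the unconstrained model by one of two forms. Either fit the mixed model with a common baseline mean (terms for time, and for group at T1 only), or fit ANCOVA of the T1 value on group and the T0 value. Report the baseline-adjusted between-arm difference at T1 with its 95% confidence interval as the treatment effect.

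This does not apply to measures taken only after the intervention (System Usability Scale, treatment satisfaction) or to categorical outcomes such as stenosis grade and pain location.

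The cost is a change of wording in the statistical analysis section or the analysis plan. No further data, participants or software are needed. The sample size can stay as it is: with adjustment, power at 29 per arm is at least about 86% under the stated inputs, whatever the correlation.

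### The planned mixed model does not adjust for the baseline score, so the 12-week comparison gives up precision that data already collected could supply

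*Protocol article*

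**What the plan says.** Statistical analysis in the protocol article applies a linear mixed model to a list of questionnaire scores. Participants enter as random effects, and "the groups, the times, and the interaction between them will be regarded as fixed effects". The section mentions no baseline covariate and no constraint that the arms share a baseline mean.

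Data collection gives two assessments, T0 before the intervention and T1 after the initial 12 weeks. Primary outcome measures counts baseline among the times of the primary outcome. T0 is therefore a response in the model, with its own free group difference.

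Sample size rests on a different contrast. It was calculated "based on the difference between two means using the *T*-test, after a 12-week pilot study with 20 participants", with "10 in the control group (CG) (2.8 ± 1.9") and "10 in the intervention group (IG) (1.41 ± 1.50"). It concludes that "a total number of 58 participants (29 IG and 29 CG) will be needed", "assuming an alpha level of 0.05 and 80% power of the test". No T0 term and no T0-T1 correlation enter that calculation.

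**The concern.** With two time points and complete data, the group-by-time term in this model is the difference between arms in mean T1 minus T0. That takes the T0 score off with a coefficient fixed at 1, whatever its real relation to T1. If the analyst reads off the group difference at T1 instead, T0 plays no part in the estimate. In both cases a chance T0 difference is treated as a quantity to be estimated freely, although randomisation makes its expectation zero.

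At stake is precision in a trial of 58 women. The interaction can be less powerful than the T1 comparison that justified the sample size, and either contrast is generally less precise than an analysis adjusted for T0. This applies to every score collected at both times, not only the incontinence outcome.

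**Working it through.** **The plan's own figure.** The difference is 2.8 − 1.41 = 1.39. The pooled SD is √((1.9² + 1.50²)/2) = √2.93 = 1.712, so d = 1.39/1.712 = 0.812. A two-sided t-test at 0.05 with 80% power needs 25 per arm (50 in total), so the stated 58 does not follow from these inputs. (Sidedness is not stated; two-sided is assumed.) At 29 per arm the T1-only t-test has 86.0% power. That discrepancy is a separate matter, but it means that the trial starts with some margin over 80%.

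**What the model estimates.** One complete data set was simulated with 29 per arm, control mean 2.8, effect −1.39, and participant and residual SDs both 1.2. The fitted group-by-time term was −1.486 (SE 0.3604). The simple difference in mean change was also −1.486 (SE 0.3604). Adjusting T1 for T0 in the same data gave SE 0.3347.

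**Residual SD for each contrast**, with SD0 and SD1 the SDs at T0 and T1 and r their correlation:

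- T1 only: SD1
- Change (interaction): √(SD0² + SD1² − 2·r·SD0·SD1), which is SD1·√(2(1 − r)) when the SDs are equal
- T0-adjusted: SD1·√(1 − r²)

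The change variance minus the adjusted variance is (SD0 − r·SD1)². It is never negative, and it is zero when r = SD0/SD1.

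**Example at r = 0.4, equal SDs.** Change: 1.712 × √1.2 = 1.875, standardised effect 1.39/1.875 = 0.741, power 79.2%. Adjusted: 1.712 × √0.84 = 1.569, standardised effect 0.886, power 91.2%.

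**Power at 29 per arm** (noncentral t, two-sided 0.05, difference 1.39, SD1 = 1.712, no dropout; one degree of freedom spent on the covariate in the adjusted analysis):

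| r | T1 only | T0-adjusted | Change, SD0 = SD1 | Change, SD0 = 1.4 | Change, SD0 = 1.2 |
|---|---|---|---|---|---|
| 0.2 | 86.0% | 87.3% | 67.1% | 74.6% | 78.9% |
| 0.3 | 86.0% | 89.0% | 72.9% | 79.9% | 83.6% |
| 0.4 | 86.0% | 91.2% | 79.2% | 85.5% | 88.3% |
| 0.5 | 86.0% | 93.9% | 86.0% | 90.9% | 92.8% |
| 0.6 | 86.0% | 96.7% | 92.5% | 95.6% | 96.5% |
| 0.7 | 86.0% | 98.9% | 97.5% | 98.7% | 98.9% |

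Adjusted power does not depend on SD0. The change contrast reaches 80% at r of about 0.41 with equal SDs, 0.30 with SD0 = 1.4 and 0.22 with SD0 = 1.2. Its disadvantage against adjustment disappears at r = 1.2/1.712 = 0.70 for SD0 = 1.2, and at r = 1.4/1.712 = 0.82 for SD0 = 1.4.

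**The case against.** Several objections have weight.

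- **The model is valid.** Group, time and interaction is a standard analysis of a randomised pre/post trial; it is unbiased and keeps its type I error. This stands, so the point is about efficiency only. It is still about something the article states, since the fixed effects are listed. An unseen analysis plan might add a baseline term, and the article cannot exclude that.
- **The contrast is not named.** Sample size speaks of a group difference after 12 weeks. If the T1 contrast is the one used, power on the pilot inputs is 86% and no shortfall arises. This stands too, but that contrast is also unadjusted and gains from the same change at any useful r.
- **Two variables are involved.** The model is applied to the ICIQ-SF score, a name that the article elsewhere gives to the 0-21 total, whereas sizing used the single 0-5 frequency item. The link to the planned power is therefore an assumption. The Abstract, which says that mixed effects analysis will compare results, makes it reasonable.
- **Eligibility works in both directions.** "The study will consist of participants with UI after radiotherapy and/or brachytherapy", so zero is excluded at T0 on the screening question. A reader might infer that this lowers r and so produces a shortfall. The same restriction may also narrow the T0 SD, which helps the change score, and the documents do not show which effect is larger.

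A reader might also infer that the planned model gives wider intervals at every correlation. That holds under equal SDs for any r below 1. In general the two analyses tie when r = SD0/SD1.

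**Conclusion.** The point holds as an avoidable loss of efficiency. The model uses T0 as a second response with a free group difference, and neither contrast it offers adjusts for T0. On the stated pilot values, with equal SDs, no dropout and the model serving the frequency item, T0 adjustment raises power at r = 0.3 to 0.6 from 73-93% (interaction) or 86% (T1 only) to 89-97%.

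A reader might conclude that the trial is underpowered or that its estimate is biased. The documents support neither. Under randomisation the interaction is unbiased. A fall below 80% requires that the interaction is the chosen contrast and that r is below about 0.41, or below about 0.30 or 0.22 if the T0 SD is 1.4 or 1.2. Neither r nor the T0 SD is reported. The algebra is certain. The size of the gain depends on these unknowns, and the gain over the change score shrinks to nothing as r approaches SD0/SD1.

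**What to change.** In Statistical analysis, for every score collected at both T0 and T1 (including the frequency item, if it is analysed as a score), replace the group, time and interaction model with one of these:

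- T1 score modelled on group and T0 score; or
- a constrained longitudinal model with one common T0 mean for both arms and an unstructured 2×2 covariance, which also keeps women who have only a T0 assessment.

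Report the adjusted 12-week difference between arms with its 95% confidence interval. The System Usability Scale has no T0 value and is not affected.

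The cost is a change of wording. It needs no new data and no more participants, and the planned software can fit the analysis. The change should be recorded before any outcome data are examined by arm.
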